#### 4.6.3 *Exploratory Efficacy Analyses*

No analyses of exploratory variables will be performed.

### 4.7 **Safety Analyses**

#### 4.7.1 *Exposure of Study Drug*

IP exposure and compliance will be summarized for safety population.

#### 4.7.2 *Adverse Events*

AEs will be summarized for safety population.

A summary of subjects reporting at least one of the following AEs will be presented in an overview table:

- Any AE
- Any SAE
- Any treatment-related AE
- Any treatment-related SAE
- Any AE leading to discontinuation
- Death

Summaries per SOC and PT presenting n (%) of AEs and n (%) of subjects with at least one AE will be provided for:

- All AEs (includes all serious and non-serious AEs)
- All AEs by maximum reported intensity
- All AEs by causality
- All SAEs
- All AEs leading to discontinuation

## 5 **INTERIM ANALYSES**

After the first 10 subjects have been treated, pharmacokinetic analyses were performed with respect to fatty acid concentrations in serum.

After the first 30 subjects have been treated and evaluated a safety data committee performed an evaluation to confirm that the safety profile is acceptable and that the assumption of a reduction in ROP incidence is reasonable.

|                                     |  |                                    |               |
|-------------------------------------|--|------------------------------------|---------------|
| STATISTISKA KONSULTGRUPPEN          |  | Statistical Analysis Plan          |               |
| Protocol:
Mega Donna Mega |  | Protocol No:
MEGADONNAMEGA 16-7 |               |
|                                     |  | Version:
1.0                    | Page 20 of 21 |

## 6 CHANGES OF ANALYSIS FROM PROTOCOL

No changes to protocol version 7b have been done. However, no detailed description of the analyses were available in the protocol. All analyses specified within this SAP are aimed to be conservative regarding the IP and applying ICH and EMA guidelines for statistical analyses and adjustments. Additionally, recently published guidelines from ASA and NEJM have been employed.

## 7 LISTING OF TABLES AND FIGURES

### 7.1 Listing of Tables

| Table Number | Table Title                                                                                              |
|--------------|----------------------------------------------------------------------------------------------------------|
| 14.1.1       | Patient Disposition and Data Sets Analyzed (ITT Population)                                              |
| 14.1.2       | Protocol Deviations Leading to Exclusion from PP Population (ITT Population)                             |
| 14.1.3.1     | Demographics and Baseline Characteristics (ITT Population)                                               |
| 14.1.3.2     | Demographics and Baseline Characteristics (PP Population)                                                |
| 14.1.6.1     | Prior Medications (ITT population)                                                                       |
| 14.1.6.2     | Concomitant Medications (ITT population)                                                                 |
| 14.2.1.1     | Primary Efficacy Analysis (ITT Population)                                                               |
| 14.2.1.2     | Analysis of Primary Efficacy Variable (PP Population)                                                    |
| 14.2.x       | Other efficacy variables/analyses                                                                 |
| 14.2.x       | Exploratory Analysis – xxx                                                                        |
| 14.3.1.1     | Duration of Exposure and Compliance (Safety Population)                                                  |
| 14.3.2.1     | Summary of Adverse Events (Safety Population)                                                            |
| 14.3.2.2     | Adverse Events, by System Organ Class and Preferred Term (Safety Population)                             |
| 14.3.2.3     | Adverse Events, by System Organ Class, Preferred Term and Maximum Reported Intensity (Safety Population) |
| 14.3.2.4     | Adverse Events, by System Organ Class, Preferred Term and Causality Assessment (Safety Population)       |
| 14.3.2.5     | Serious Adverse Events, by System Organ Class and Preferred Term (Safety Population)                     |
| 14.3.3       | Adverse Events Leading to Discontinuation, by System Organ Class and Preferred Term (Safety Population)  |

### 7.2 Listing of Figures

| Figure Number | Figure Title                                                                  |
|---------------|-------------------------------------------------------------------------------|
| 14.2.1.1      | Cumulative Incidence Curve for Severe ROP by Treatment Group (ITT Population) |
| 14.2.1.2      | Cumulative Incidence Curve for Severe ROP by Treatment Group (PP Population)  |
| 14.2.2.1      | AA Profile by Treatment Group (ITT Population)                                |
| 14.2.2.2      | AA Profile by Treatment Group (PP Population)                                 |
| 14.2.3.1      | DHA Profile by Treatment Group (ITT Population)                               |

|                                     |  |                                    |               |
|-------------------------------------|--|------------------------------------|---------------|
| STATISTISKA KONSULTGRUPPEN          |  | Statistical Analysis Plan          |               |
| Protocol:
Mega Donna Mega |  | Protocol No:
MEGADONNAMEGA 16-7 |               |
|                                     |  | Version:
1.0                    | Page 21 of 21 |

|            |                                                                        |
|------------|------------------------------------------------------------------------|
| 14.2.3.2   | DHA Profile by Treatment Group (PP Population)                         |
| 14.2.4.1   | BPD, IVH Grade and PDA by Treatment Group (ITT Population)             |
| 14.2.4.2   | BPD, IVH Grade and PDA by Treatment Group (PP Population)              |
| 14.2.5.1   | Cumulative Incidence Curve for NEC by Treatment Group (ITT Population) |
| 14.2.5.2   | Cumulative Incidence Curve for NEC by Treatment Group (PP Population)  |
| 14.2.6.1.x | XXXX Development Curves by Treatment Group (ITT Population)            |
| 14.2.6.2.x | XXXX Development Curves by Treatment Group (PP Population)             |
| 14.3.1     | Summary of Adverse Events (Safety Population)                          |

|                                     |  |                                    |              |
|-------------------------------------|--|------------------------------------|--------------|
| STATISTISKA KONSULTGRUPPEN          |  | Statistical Analysis Plan          |              |
| Protocol:
Mega Donna Mega |  | Protocol No:
MEGADONNAMEGA 16-7 |              |
|                                     |  | Version:
1.0                    | Page 1 of 21 |

### 1. Definition of Safety population

**Original definition:** All enrolled subjects who received at least one dose of randomized investigational product will be included in the safety population.

**Extended definition to be used in the study report:** All randomized infants will be included in the safety population, since all infants are treated according to regular clinical practice, both those randomized to Formulaid and those randomized to not receive Formulaid.

### 2. Applied inclusion criteria to PP population

**Original definition:** All randomized subjects with no major protocol violations will be included in the Per Protocol (PP) population. The final decisions regarding the PP population will be taken at the Clean File meeting before the database lock.

Major protocol violations will be at least following, but not limited to those:

- Final ROP stage available

Compliance to medication will be evaluated for all infants during the treatment period and sub-periods and appropriate cut-off will be applied. The final decision will be made at the clean file meeting before the database lock.

**Extended definition:** Beside final ROP stage available, an additional bullet point for the PP population added during the clean file meeting was the compliance to investigational product of  $\geq 70\%$ .

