### **11.1 Determination of Sample Size and Statistical Methods**

#### **Primary endpoint**

The mean incidence of any ROP in an age-matched population (22 weeks + 0 days to 27 weeks + 6 days of GA at birth) in Sweden during the years 2008 – 2012 is calculated to 42%. Assuming an alpha of 5%, a power of 80% and a 50% reduction in incidence of any ROP, i.e. from 42% to 22%, a sample size of 80 subjects per treatment group is required. The reduction in any ROP with AA:DHA supplementation is based on efficacy in previous publications (33).

A total of 105+105 subjects will be included to compensate for protocol violations (experience gained in pilot study) and drop-outs (e.g. a perinatal death rate of approximately 15% at these gestational ages).

After the first 10 subjects have been treated, we will perform pharmacokinetic analyses with respect to fatty acid concentrations in serum.

After the first 30 subjects have been treated and evaluated a safety data committee will perform an evaluation to confirm that the safety profile is acceptable and that the assumption of a reduction in ROP incidence is reasonable.

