### 1.4 Sample Size

The sample size text below is provided in the study protocol version 7b.

The mean incidence of any ROP in an age-matched population (22 weeks + 0 days to 27 weeks + 6 days of GA at birth) in Sweden during the years 2008 – 2012 is calculated to 42%. Assuming an alpha of 5%, a power of 80% and a 50% reduction in incidence of any ROP, i.e. from 42% to 22%, a sample size of 80 subjects per treatment group is required. The reduction in any ROP with AA:DHA supplementation is based on efficacy in previous publications.

A total of 105+105 subjects will be included to compensate for protocol violations (experience gained in pilot study) and drop-outs (e.g. a perinatal death rate of approximately 15% at these gestational ages).

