#### 2.1.2 Per-Protocol Population

All randomized subjects with no major protocol violations will be included in the Per Protocol (PP) population. The final decisions regarding the PP population will be taken at the Clean File meeting before the database lock.

Major protocol violations will be at least following, but not limited to those:

- Final ROP stage available

|                                     |  |                                    |               |
|-------------------------------------|--|------------------------------------|---------------|
| STATISTISKA KONSULTGRUPPEN          |  | Statistical Analysis Plan          |               |
| Protocol:
Mega Donna Mega |  | Protocol No:
MEGADONNAMEGA 16-7 |               |
|                                     |  | Version:
1.0                    | Page 12 of 21 |

- Compliance to medication will be evaluated for all infants during the treatment period and sub-periods and appropriate cut-off will be applied. The final decision will be made at the clean file meeting before the database lock.

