## 4 STATISTICAL METHODOLOGY

### 4.1 General Methodology

For continuous variables mean, Standard Deviation (SD), median, minimum and maximum will be presented, or median and Interquartile Range (IQR) as applicable, and for categorical variables number and percentage.

The baseline characteristics will be described; inferential statistics will be performed and interpreted descriptively only.

The confirmatory analyses will be only performed for:

1. Primary efficacy variable, impact of IP on severe ROP (comparison of event rates)
2. Secondary efficacy variable, impact of IP on overall levels of AA (mol%) continuously over time
3. Secondary efficacy variable, impact of IP on overall levels of DHA (mol%) continuously over time
4. Secondary efficacy variable, impact of IP on BPD (yes/no at PMA week 36, comparison of event rates)
5. Secondary efficacy variable, impact of IP on IVH (grade 0-4)

For those analyses the difference in the estimates and their 95% Confidence Intervals (CI) will be provided, and tests will be adjusted for multiplicity according to the fix sequential method as per the sequential order above. This methods allows for the significance mass of 0.05 to be inherited to the next variable in order and the testing is stopped when non-significance is achieved.

|                                     |  |                                    |               |
|-------------------------------------|--|------------------------------------|---------------|
| STATISTISKA KONSULTGRUPPEN          |  | Statistical Analysis Plan          |               |
| Protocol:
Mega Donna Mega |  | Protocol No:
MEGADONNAMEGA 16-7 |               |
|                                     |  | Version:
1.0                    | Page 17 of 21 |

Missing data will be handled according to the section 3.2.

All other analyses will be considered as exploratory, 95% CI will be provided for the difference between the groups and p-values will be given only for descriptive purpose.

All tests will be two-tailed and confirmed analyses will be conducted at 0.05 level applying fix sequential testing. All analyses will be performed using SAS software version 9.4 (SAS Institute Inc., Cary, NC, USA).

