Main analyses will be performed on ITT population and robustness analyses on PP population. Sensitivity analyses performed on ITT population handling deaths and early drop-outs as per the section 3.2 will also be performed.

|                                     |  |                                    |               |
|-------------------------------------|--|------------------------------------|---------------|
| STATISTISKA KONSULTGRUPPEN          |  | Statistical Analysis Plan          |               |
| Protocol:
Mega Donna Mega |  | Protocol No:
MEGADONNAMEGA 16-7 |               |
|                                     |  | Version:
1.0                    | Page 19 of 21 |

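### The single per-protocol set requires a final ROP stage, so the PP repeats for NEC, IVH, PDA and BPD leave out infants who die before any ROP staging

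*Combined protocol and SAP*

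**What the plan says.** SAP 2.1.2 admits to the PP set all randomised infants without major violations. The first item in its list of violations is "Final ROP stage available". As a violation this reads the wrong way round, but item 2 of the supplementary note to the SAP (Applied inclusion criteria to PP population) settles the meaning: "Beside final ROP stage available, an additional bullet point for the PP population added during the clean file meeting" was compliance of at least 70%. An available final ROP stage is therefore a condition of entry. No endpoint-specific PP set is defined anywhere.

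SAP 4.6.2 closes the secondary analyses with "Main analyses will be performed on ITT population and robustness analyses on PP population". SAP 7.2 lists the resulting outputs: Figure 14.2.4.2 for BPD, IVH grade and PDA in the PP set, and Figure 14.2.5.2, "Cumulative Incidence Curve for NEC by Treatment Group (PP Population").

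On timing, protocol 8.1 starts ROP examinations at five to six weeks of age and not before PMA 31 weeks. Protocol 6.3 and SAP 3.2.1 say four to five weeks of age. SAP 3.2.2 describes IVH and PDA as assessed early after birth. SAP 1.4 expects "a perinatal death rate of approximately 15% at these gestational ages".

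**The concern.** A final ROP stage is an evaluability condition for ROP. It has no rationale for NEC, IVH or PDA, and it is settled after randomisation, partly by whether the infant survives. An infant who received every dose and died in week three with NEC has a recorded event and no protocol violation, yet leaves the PP set because there is no ROP stage.

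This selection does not come from the compliance rule. SAP 3.3.1 measures compliance as days on product divided by days in study, so an infant who dies early can meet the 70% cut-off.

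At stake is what the PP repeat can be used for. The SAP offers it as a robustness check on the ITT result. For NEC, IVH and PDA it conditions on surviving to ROP staging, which the event itself may prevent. In the PP cumulative incidence curve for NEC, early death, the competing event, is removed by construction. Agreement or disagreement between ITT and PP is then hard to interpret. The matter deserves attention because NEC is a gut outcome in a trial of an enteral product, IVH is in the confirmatory sequence, and the ITT sensitivity rules for deaths with missing IVH or PDA still carry question marks in SAP 3.2.2.

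**Working it through.** **1. The plan's own figure.** Inputs: "Assuming an alpha of 5%, a power of 80% and a 50% reduction in incidence of any ROP, i.e. from 42% to 22"%, and "All tests will be two-tailed" (SAP 4.1). The plan's result: "a sample size of 80 subjects per treatment group is required". With unpooled variance, n = (1.960 + 0.842)² × (0.42 × 0.58 + 0.22 × 0.78) / 0.20² = 81.5, so 82 per arm. The pooled formula gives 85, and power at 80 per arm is 0.78. The figure of 80 is reproduced to within two infants by the unpooled formula. Nothing below depends on it.

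**2. Who cannot have a ROP stage.** Under protocol 8.1, an infant born at 22+0 weeks is first examined at PMA 31+0, at 31 − 22 = 9 weeks of age. An infant born at 27+6 is first examined at five to six weeks of age, at PMA 32+6 to 33+6. Under protocol 6.3 and SAP 3.2.1 the first examination is at four to five weeks for everyone. On any of these schedules, a death in the first four weeks leaves no ROP stage, while IVH and PDA, and any NEC that has occurred, may already be recorded. Every first examination falls before PMA 36 weeks, so an infant who dies before staging has not reached the BPD assessment and no observed BPD event is lost.

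**3. How many infants.** 0.15 × 105 = 15.75 per arm, or 31.5 of 210. This leaves at most 105 − 15.75 = 89.25 per arm before the compliance cut-off. It assumes that the 15% applies to randomised infants and that every such death precedes staging. If only half did, the loss would be 15.75 of 210.

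**4. Effect on a NEC rate in one arm.** The documents give no NEC rate or case fatality, so both are assumed. With 15% deaths before staging:

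PP risk = NEC risk × (1 − fatal share) / (1 − 0.15)

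| Assumed NEC risk | No NEC fatal before staging | 25% fatal | 50% fatal |
|---|---|---|---|
| 5% | 5.9% | 4.4% | 2.9% |
| 10% | 11.8% | 8.8% | 5.9% |
| 15% | 17.6% | 13.2% | 8.8% |

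The PP rate can lie above or below the ITT rate.

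**5. Effect on the NEC risk ratio.** Assumed control arm: NEC 12%, 40% of it fatal before staging. Fatal NEC is then 4.8%, non-fatal NEC 7.2%, other deaths 10.2% and all deaths 15%. Control PP risk = 7.2/85. Other deaths are held at 10.2% in the treated arm.

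- *Only fatal NEC doubles (9.6%).* ITT: (9.6 + 7.2)/12 = 1.40. Deaths are 19.8%. PP: (7.2/80.2)/(7.2/85) = 1.06.
- *Only fatal NEC halves (2.4%).* ITT: (2.4 + 7.2)/12 = 0.80. Deaths are 12.6%. PP: (7.2/87.4)/(7.2/85) = 0.97.
- *All NEC rises by 1.40 with fatality still 40%.* NEC is 16.8%: fatal 6.72%, non-fatal 10.08%. ITT: 1.40. Deaths are 16.92%. PP: (10.08/83.08)/(7.2/85) = 1.43.

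The PP ratio is pulled strongly towards 1 when the effect is confined to fatal cases. At constant case fatality it is not.

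**The case against.** The strongest reply is that nothing decisive uses the PP set. SAP 4.6.2 makes ITT the main analysis. The fixed sequence in SAP 4.1 gives PP no role, and NEC and PDA are outside that sequence. NEC also has a competing-risk sensitivity analysis on ITT (Gray's test and, under Note-to-SAP 1, Fine and Gray) and an ITT cumulative incidence figure, 14.2.5.1. NEC and IVH are classified adverse events, deaths are tabulated, and the supplementary note extends the safety set to all randomised infants. A reader can see a gap between ITT and PP. All of this stands and limits the weight of the point.

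Three further objections also stand in part. First, the final ROP stage is not defined for an infant who dies partway through weekly screening, so exclusion is certain only for deaths before any staging. Secondly, the 15% is a perinatal death rate, not a rate of death before staging. Thirdly, BPD differs from the other three endpoints because no observed event is deleted.

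Two stronger readings are tempting. A reader might infer that the trial's NEC and IVH results as a whole lose their fatal cases. The documents do not support this, because only the PP repeats are affected. A reader might also infer that the PP result must look null or reassuring. Working step 5 shows that this depends on how any effect divides between fatal and non-fatal cases, on which the documents are silent.

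What the reply does not answer is why an ROP evaluability condition should govern a robustness check on NEC, IVH or PDA.

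**Conclusion.** The point holds for the PP robustness analyses of NEC, IVH, PDA and BPD and goes no further. It is a minor-to-moderate flaw. For NEC, IVH and PDA, observed events in infants who die before ROP staging are dropped. For BPD, infants who die before PMA 36 weeks change from non-events to excluded. The PP curve for NEC is conditional on survival to staging.

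The size is up to about 31 or 32 of 210 infants, on the assumption that all of the roughly 15% deaths occur after randomisation and before staging. The size and direction of any bias in a treatment comparison cannot be fixed from the documents, because neither deaths nor case fatality by arm are given. The risk ratios above show a possible range, not a prediction.

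**What to change.** - Make an available final ROP stage a condition only for the PP analysis of severe ROP.
- For NEC, IVH, PDA and BPD, define a second PP flag from the other major-violation criteria, including the compliance cut-off. Keep infants who died, scored to their last observation.
- Treat death as a competing event in the PP curve for NEC.
- Label Figures 14.2.4.2 and 14.2.5.2 with the set used.
- State what counts as a final ROP stage for an infant who dies during screening.
- If the PP outputs already exist, re-run these and disclose that the change was made after the clean file meeting.

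The cost is a further note to the SAP, a second flag in the analysis dataset and the re-run outputs. No new data are needed. The drawbacks are two PP sets to report and explain, and the reopening of a decision taken at the clean file meeting.

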### 3. Clarification on the analysis fatty acid secondary variable

**Original definition:** Postnatal serum fatty acid (in mol%) composition in preterm infants with and without AA:DHA supplementation (at 0h, 72h, day 7, day 14, every second week until PMA of 29 weeks and thereafter at 30, 32, 34, 36, 40 weeks PMA) will be analysed as secondary variable. Missing data will not be imputed, analysis will be performed using Mixed Models for Repeated Measures (MMRM) where missing data at random is assumed.

**Clarification:** Due to infants are born in different gestational weeks, serum fatty acid data for postnatal weeks 4 and 6 will be available only for a proportion of infants, those with the lowest gestational age at birth. Therefore postnatal weeks 4 and 6 will be only described but not used in planned MMRM analyses.

|                                     |                                    |               |  |
|-------------------------------------|------------------------------------|---------------|--|
| STATISTISKA KONSULTGRUPPEN          |                                    | Note-to-SAP 1 |  |
| Protocol:
Mega Donna Mega | Protocol No:
MEGADONNAMEGA 16-7 |               |  |
|                                     | Version:
1.0                    | Page 1 of 2   |  |

---

**SPONSOR:** [name]

**STUDY:** Mega Donna Mega

**TO:** SAP version 1.0 dated 19 November 2019

**DATE:** 14 April 2020

**SUBJECT:** Note-to-file to SAP - Clarifications

---

Following clarifications were not defined in detail in the final SAP and are documented in this note-to-file.

